### Participants

Patient enrollment started in October 2015. Patients are identified at the two hospital facilities. Criteria for the diagnosis ACNES are (1) a constant site of tenderness that is superficially located covering a fingertip-sized point of maximal pain at the lateral border of the rectus abdominis muscle, (2) a somewhat larger area of altered skin sensation covering this tender point and (3) observing that tenderness increases by abdominal muscle tensing using Carnett’s test [13, 14]. Only adult patients (over 18 years old) diagnosed with unilateral ACNES and having temporary success from an injection regimen will be invited for participation. In ACNES, a treatment regimen consists of local abdominal wall infiltration using 5–10 mL lidocaine as described in our earlier studies [4, 15]. “Temporary” is defined as having more than 50% pain reduction for at least 1 week after such a local infiltration although symptoms recur afterwards (refractory ACNES). Sixty-six patients (male or female) will be enrolled in the trial. Patients are not eligible if pain is caused by surgical scar-related pain syndromes (i.e., point of maximum pain is located at the site of a surgical scar) or due to recent intra-abdominal pathology. Presence of other chronic pain syndromes including fibromyalgia, dystrophy, chronic low back pain, impaired communication, a previous spinal surgical procedure at or between vertebral levels T7 and L1 are also exclusion criteria. A full list of inclusion and exclusion criteria is given in Table 1. Once eligibility is determined, patients are counseled on the specifics of the study and are given a number of days prior to providing consent.

**Table 1 Tab1:** Subject inclusion and exclusion criteria

Inclusion criteria	Exclusion criteria
• Patient is diagnosed with unilateral anterior cutaneous nerve entrapment syndrome (ACNES)	• Patient has surgical scar-related pain syndromes
• Eligible for neurectomy (i.e., having temporarily success using injection therapy)	• Patient has recent intra-abdominal pathology
• Patient >18 years old	• Patient has other chronic pain syndromes (such as fibromyalgia, dystrophy, chronic low back pain)
• Patient is able to provide written informed consent	• Patient has other neuropathic diseases
• Patient is willing to participate in the follow-up schedule and protocol	• Patient has impaired communication
	• Patient has participated in another clinical investigation within 30 days

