**Fig. 3 Fig3:**
[figure not shown]
Content for the schedule of enrollment, interventions and assessments, according to the Standard Protocol Items: Recommendations for Interventional Trials (SPIRIT) Statement [12]

Secondary outcomes include the effect of PRF or neurectomy on quality of life, disability, neuropathic characteristics, medication usage and satisfaction. The Short Form Health Survey-12 questionnaire (SF-12) is used for measuring quality of life and interference from pain [17]. Patient disability will be measured with the Pain Disability Index (PDI) and the Brief Pain Inventory (BPI) [18, 19]. The Douleur Neuropathique (DN4) is used in order to discriminate between neuropathic and non-neuropathic pain [20]. Medication usage prior to, and after, treatment will be recorded using World Health Organization (WHO) pain steps. Patient satisfaction is recorded using the Patient Global Impression of Change (PGIC, 1 very much worse to 7 very much improved) and Verbal Rating Scales methodology (VRS, 1 = “I am very satisfied” and 5 = “Pain is worse after treatment”) [4, 21].

All adverse events (AEs) reported spontaneously by the patient, or observed by the investigators or their staff, will be recorded.

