### Statistical methods

All analyses are performed using the Statistical Package for the Social Sciences (SPSS) version 21 for Windows. Categorical variables are described as frequencies. Continuous data are tested for normality and are presented as means with standard deviation (±SD) or median values (range) as appropriate. The primary outcome measure is pain relief using the NPRS as compared to the preintervention pain levels (t_0_). Data of the PRF and neurectomy groups will be compared using the Student’s *t* test or the Wilcoxon signed-rank test, as appropriate. Secondary outcomes will be compared between groups at various time points (baseline, 8-week follow-up and 6-month follow-up). They will be compared to preintervention values using Student’s *t* test or the Wilcoxon signed-rank test as appropriate. A *p* value < 0.05 is considered significant. Analysis of data will be done as randomized (the intention-to-treat analysis) and secondary “as-treated.”

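### Secondary outcomes: the baseline tests and, as naturally read, the before-after tests do not estimate PRF versus neurectomy, and two outcomes have no pre-intervention value

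*Protocol article*

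**What the plan says.** All references are to the Methods of the protocol article.

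- **Outcomes** sets the scope: "Secondary outcomes include the effect of PRF or neurectomy on quality of life, disability, neuropathic characteristics, medication usage and satisfaction". The instruments named are SF-12, PDI, BPI, DN4, WHO pain steps, PGIC and a satisfaction VRS.
- The same section describes the last two: "Patient satisfaction is recorded using the Patient Global Impression of Change (PGIC, 1 very much worse to 7 very much improved"), and a VRS whose worst category is "Pain is worse after treatment".
- **Statistical methods** gives two instructions for these outcomes, one after the other: "Secondary outcomes will be compared between groups at various time points (baseline, 8-week follow-up and 6-month follow-up). They will be compared to preintervention values". The tests named for the second are Student's t test or the Wilcoxon signed-rank test. No outcome is exempted from either.
- The same section then sets one general rule for all analyses: a p "value < 0.05 is considered significant".
- **Randomization** states that patients are allocated after the baseline questionnaires have been filled in.

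**The concern.** Three features of this short passage do not fit the trial's question, which is how PRF compares with neurectomy.

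1. Baseline is one of the time points at which the arms are compared under the 0.05 rule. Those scores are recorded before allocation, so treatment cannot have influenced them.
2. A comparison with pre-intervention values, read as a before-after test, asks whether patients changed. It does not ask whether one treatment changed them more than the other. Both arms are active, nobody is blinded and no arm is untreated, so a before-after p-value cannot separate a treatment effect from any other cause of change.
3. The PGIC asks for an impression of change and the VRS for satisfaction after treatment. Neither can be answered before treatment, so the second instruction cannot be followed for them.

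At stake is how the secondary results are read. The design expects fewer responders with PRF (30% against 70%), while the Discussion asks whether PRF is effective. A significant before-after result on quality of life or disability could be taken as support for PRF without any randomised comparison behind it.

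**Working it through.** **The plan's own figure.** The sample size reproduces. For 70% versus 30% responders, 80% power and two-sided 5%, the continuity-corrected formula gives 29 per arm, or 58 in total. Then 58/0.9 = 64.4, which rounds up to 65, and to 66 for equal arms. The point below does not touch this figure; it supplies n = 29 per arm.

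**Which instruments have a pre-intervention value**

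| Instrument | Pre-intervention value? | Basis |
|---|---|---|
| SF-12, PDI, BPI, DN4 | Yes | State at the time of asking; taken as part of the baseline questionnaires |
| WHO pain step | Yes, ordinal | Outcomes records it before and after treatment |
| PGIC | No | Anchors run from worse to improved |
| Satisfaction VRS | No | Anchors refer to the result of treatment |

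The instruction to compare with pre-intervention values can be carried out for five of the seven instruments.

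**Baseline tests.** Five instruments have a baseline value. Assuming one test each, independent, the chance of at least one p<0.05 is 1 − 0.95^5 = 0.226. In a simulation with correlated outcomes (29 per arm, 3,000 runs, assumed correlation 0 to 0.7 between outcomes and 0.5 between visits) it is 22% down to 15%. With sound allocation every such result is chance.

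**Before-after tests.** A paired t test with n = 29 reaches p<0.05 when the mean change exceeds t(0.975, 28)/√29 = 2.048/5.385 = 0.380 SD of the change scores. The formula contains nothing about the other arm.

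The same simulation, with outcome correlation 0.5 and the same shift added to both arms after baseline, shows what follows. There is no difference between arms in any row, and the shifts are assumptions chosen to show the mechanism.

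| Common shift (SD) | Share of before-after tests with p<0.05 | At least one of 14 post-treatment between-arm tests with p<0.05 |
|---|---|---|
| 0 | 5% | 39% |
| 0.2 | 18.5% | 41% |
| 0.3 | 35% | 38% |
| 0.5 | 74% | 37% |

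The before-after tests respond to a shift shared by both arms. The between-arm tests do not, apart from simulation noise.

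**Number of tests, for context only.** Seven instruments at two post-treatment visits make 14 between-arm tests. If independent, 1 − 0.95^14 = 0.512. With outcome correlation from 0 to 0.7 the simulation gives 49% down to 32%.

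**The case against.** The best defence is that the sentence on pre-intervention values may not mean a before-after test. The primary outcome is also described as pain relief relative to pre-intervention level and is then compared between arms, so the secondary sentence could mean change from baseline compared between arms. Naming the signed-rank test does not settle it, because the same section names that test for the between-arm primary comparison. This stands to the extent that a before-after test within each arm is an inference. But the text gives between-arm comparison its own sentence and then adds the second one, so before-after is the more natural reading. On either reading PGIC and VRS have no value to compare with.

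Second, baseline p-values alter no treatment estimate, and a score that does not exist cannot yield a false result. The assessment schedule in Fig. 3 is not shown and may place PGIC and VRS after treatment only. All this limits the harm, but the analysis text still needs to match the instruments.

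Third, these are secondary outcomes in a trial described as proof-of-concept, and between-arm secondary comparisons are planned. Nothing in the article says that before-after p-values will be read as effects of PRF relative to neurectomy. That stands, and it keeps the point modest.

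Fourth, a multiplicity rule for secondary outcomes may sit in an analysis plan that is not shown. That stands too: its absence here is no finding.

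**Conclusion.** The point holds as one about the choice and wording of secondary analyses. The baseline tests are uninformative. The pre-intervention comparison cannot be made for two of seven instruments and, on its natural reading, does not address the randomised question for the other five. The primary endpoint and the sample size of 58 (66 with attrition) are not affected.

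Two stronger conclusions might be inferred, and the documents support neither.

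- *Spurious significant findings are near certain.* The 51% figure needs 14 independent tests; with correlated outcomes it is about 32–49%. Near certainty arises only by assuming a sizeable shift in both arms and reading before-after p-values as treatment effects, or by treating the overlapping as-treated analyses as independent. The count of tests does not carry this point.
- *Regression to the mean will by itself produce significant improvement.* Patients do enter after relapse ("although symptoms recur afterwards (refractory ACNES"), but the eligibility criteria set no minimum pain score, and the article gives no figure for natural course. The documents do not show how large any such shift would be. The 0.38 SD threshold also cannot be turned into points on a scale, because no SD is given for any secondary instrument.

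The assumptions used are one test per instrument, 29 evaluable patients per arm, and the stated correlations.

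**What to change.** Reword the secondary-outcome part of Statistical methods as follows.

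1. Describe baseline values by arm without significance tests.
2. Show change from pre-intervention by arm descriptively, without p-values, for the instruments that have a baseline. State that PGIC and VRS are post-treatment ratings and are exempt.
3. Base inference on between-arm comparisons at 8 weeks and at 6 months. For SF-12, PDI, BPI and DN4, adjust for the baseline score.
4. Compare PGIC, VRS and WHO step between arms with the rank-sum test.
5. Read the 6-month comparison in light of the crossover open to unsuccessful PRF patients at 8 weeks. As randomised, it compares PRF with optional later neurectomy against neurectomy from the start.
6. Say that secondary p-values are supportive.

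If a between-arm comparison of change was intended all along, items 2 and 3 only make that explicit. The cost is a few sentences and fewer tests: no new data, visits or patients. The sponsor gives up calling a before-after change in a secondary outcome significant.

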**Methods:**

Adult ACNES patients having short-lived success following injections are randomized to PRF or neurectomy. At the 8-week follow-up visit, unsuccessful PRF patients are allowed to cross over to a neurectomy. Primary outcome is pain relief after either therapy. Secondary outcomes include patient satisfaction, quality of life, use of analgesics and unanticipated adverse events. The study is terminated 6 months after receiving the final procedure.

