## Methods

### Trial design

This prospective, multicentre, non-blinded, proof-of-concept, randomized controlled trial (with a one-way optional crossover at 8 weeks) is performed in the SolviMáx Center of Expertise for ACNES and Center of Excellence for Abdominal Wall and Groin Pain and Maasziekenhuis Pantein, Boxmeer, The Netherlands. SolviMáx is a subdivision of the Surgical Department of Máxima Medical Center (MMC), a teaching hospital situated in the southern part of The Netherlands. The Dutch Ministry of Health, Welfare and Sport has certified SolviMáx as a Center of Expertise for ACNES treatment. The trial will be based on a clinical proof-of-concept design in order to investigate a potential difference in pain relief following either PRF treatment or an anterior neurectomy in ACNES. Furthermore, it is designed to attain more knowledge on the use of PRF on peripheral nerves and to detect possible side effects.

The present trial follows the guidelines of the Declaration of Helsinki (version 19 October, 2013). The protocol (protocol number NL53171.015.15) is approved by the Medical Ethics Committee of MMC. The study protocol (version 1) is registered at www.trialregister.nl (NTR registration number: 5131, date of registration 15 April 2015). The present paper is written according to the Standard Protocol Items: Recommendations for Interventional Trials (SPIRIT) 2013 Statement for reporting a clinical trial protocol [12]. The SPIRIT Checklist is provided as Additional file 1.

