### Outcomes

The primary objective is to compare the effect of PRF with a neurectomy in terms of pain relief at the 8-week follow-up. The outcome is measured using the Numeric Pain Rating Scale (NPRS, 0 = no pain and 10 = excruciating). Pain is measured at t_0,_ before intervention and 8 weeks after allowing the determination of short-term efficacy (t_1_) as shown in the schedule of enrollment, interventions and assessments, according to the SPIRIT Statement (Fig. 3). Long-term efficacy is measured at 6-month follow-up (t_2_). Success is defined as more than 50% NPRS pain reduction following intervention.

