### Sample size

Sample size estimation is based on a “responder” analysis, as recommended by the Initiative on Methods, Measurement and Pain Assessment in Clinical Trials (IMMPACT) Group recommendations [21]. Effect sizes were estimated on the basis of published academic literature. Neurectomy is considered successful in 70% [13, 22–25]. Regarding the potential efficacy of PRF treatment, a mean effect size was estimated at 30%. There is no available academic literature apart from two case reports on the use of PRF in ACNES patients. The targeted effect size is a difference in proportion responding to treatment (neurectomy versus PRF) of 40%; i.e., 70% responding in neurectomy the group versus 30% in the PRF group. Using G*Power 3.1.7 software, 80% power and a two-tailed alpha of 5%, 58 participants are needed to demonstrate a potential effect of either type of treatment on pain relief. With an allowance for attrition of 10% in both arms at 6-month follow-up, we will aim to recruit a total of 66 patients.

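### The secondary as-treated analysis is not limited to data before the 8-week crossover; grouping by procedure received at 6 months would bias PRF success upward

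*Protocol article*

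**What the plan says.** The Statistical methods section of the protocol article names two analyses: "Analysis of data will be done as randomized (the intention-to-treat analysis) and secondary" as-treated. It does not say how as-treated groups are formed or to which visit they apply. The same section compares secondary outcomes between groups at baseline, 8 weeks and 6 months.

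The Trial design section describes a trial "with a one-way optional crossover at 8 weeks", and the abstract says who may use it: "At the 8-week follow-up visit, unsuccessful PRF patients are allowed to cross over to a neurectomy". Uptake is not given.

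The Outcomes section places the main comparison at the crossover visit: "The primary objective is to compare the effect of PRF with a neurectomy in terms of pain relief at the 8-week follow-up". It adds a later one: "Long-term efficacy is measured at 6-month follow-up". Success is a responder criterion: "Success is defined as more than 50% NPRS pain reduction following intervention". The abstract sets the end of follow-up: "The study is terminated 6 months after receiving the final procedure". Patients who cross over are therefore followed after their neurectomy.

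**The concern.** After week 8 the procedure a patient has received depends on that patient's own outcome. Only PRF patients can switch, and only those in whom PRF failed. Grouping by procedure received at 6 months therefore takes failures out of the PRF group and adds them to the neurectomy group, while PRF successes stay where they are. That is selection on the outcome, and it raises the PRF success rate at any uptake above zero.

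The abstract says that PRF, if effective, may enter the treatment algorithm and reduce the number of operations. A 6-month as-treated table with an inflated PRF rate could be cited for that decision, although part of the figure comes from the crossover rule.

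**Working it through.** **Inputs from the protocol article.** The Sample size section assumes "70% responding in neurectomy the group versus 30% in the PRF group", 80% power, two-sided 5%, 58 patients before attrition and 66 after a 10% allowance. Randomisation is 1:1, so 33 per arm.

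**Plan's own figure.** For 0.70 versus 0.30 (mean 0.50, difference 0.40), the uncorrected size per arm is [1.96 × √(2 × 0.5 × 0.5) + 0.8416 × √(0.21 + 0.21)]² / 0.40² = 23.3, so 24. With continuity correction it is (23.3/4) × [1 + √(1 + 4/(23.3 × 0.40))]² = 28.1, so 29 per arm and 58 in total. An exact Fisher test also first holds 80% power at 29 per arm (0.814, against 0.790 at 28). For attrition, 29/0.90 = 32.2, so 33 per arm and 66. The sample size reproduces and is not in dispute.

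**Assumptions the documents do not give.**
- u: share of PRF failures who cross over.
- k: share of 8-week PRF responders still responding at 6 months.
- q: success of neurectomy after failed PRF.
- PRF failures who do not cross over remain failures.
- Neurectomy success stays at 70%.

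**Expected split of the PRF arm.** 0.30 × 33 = 9.9 responders and 0.70 × 33 = 23.1 failures.

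**As-treated rates at 6 months, by procedure received.**
- PRF: 0.30k / [0.30 + 0.70(1 − u)]
- Neurectomy: (0.70 + 0.70uq) / (1 + 0.70u)

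With k = 1 (patient numbers rounded, rates from unrounded values):

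| u | PRF group, n | PRF success | Excess over 30% | Neurectomy group, n | Neurectomy, q = 0.7 | Neurectomy, q = 0.5 |
|---|---|---|---|---|---|---|
| 25% | 27 | 36% | 6 | 39 | 70% | 67% |
| 50% | 21 | 46% | 16 | 45 | 70% | 65% |
| 75% | 16 | 63% | 33 | 50 | 70% | 63% |
| 80% | 15 | 68% | 38 | 51 | 70% | 63% |
| 90% | 12 | 81% | 51 | 54 | 70% | 62% |
| 100% | 10 | 100% | 70 | 56 | 70% | 62% |

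**Thresholds with k = 1.**
- Responders are half of the remaining PRF group when 0.70(1 − u) = 0.30, so u = 1 − 0.30/0.70 = 57%.
- PRF reads 70% when 0.30 + 0.70(1 − u) = 0.30/0.70 = 0.4286, so 1 − u = 0.1286/0.70 = 0.184 and u is about 82%.
- With q = 0.5 the two groups meet at about u = 75%: 0.30/0.475 = 63% and 0.9625/1.525 = 63%.

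**If PRF response fades (k = 0.6).** Without crossover PRF success is 0.30 × 0.6 = 18%. As-treated it reads 0.18/0.65 = 28% at u = 50%, 0.18/0.475 = 38% at u = 75%, and 0.18/0.30 = 60% at u = 100%. The bias remains, but PRF no longer reaches neurectomy: at full uptake neurectomy is 70% (q = 0.7) or 62% (q = 0.5).

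**Intention-to-treat at 6 months.** PRF-arm success is 0.30k + 0.70uq. With k = 1 and full uptake it is 0.30 + 0.70 × 0.70 = 79% against 70%, or 0.30 + 0.70 × 0.50 = 65% against 70%. This comparison keeps randomisation, but it measures PRF followed by neurectomy where needed, not PRF alone.

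**Crossover counted as PRF non-response.** The rate is 9.9/33 = 30% at every u with k = 1, and 18% with k = 0.6. It does not move with uptake.

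**The case against.** The strongest defence is that as-treated is undefined. If it means the first procedure received, or is applied only to 8-week data, the crossover moves nobody. A journal article may also leave the definition of analysis sets to the full protocol or analysis plan. This stands to the extent that the point must be conditional on grouping by procedure received at 6 months. It does not remove the point. The article names the analysis and sets no time limit on it. The crossover is the only departure from allocation built into the design, and follow-up to 6 months after the final procedure fits the by-procedure reading.

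A reader might go further and infer three things that the documents do not support:

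- *That the trial's answer could be reversed.* The primary comparison is at 8 weeks, as randomised, and crossover is offered only at that visit. The as-treated analysis is labelled secondary.
- *That the PRF group would consist mainly of responders.* This needs uptake above about 57%. Crossover is optional and its uptake is not stated.
- *That PRF would look as good as surgery.* This needs about 82% uptake (about 75% with q = 0.5) and lasting PRF response.

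The 30% is also the protocol's own estimate. The article cites only two case reports of PRF in this condition, so 30% is a planning value and not a known truth.

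It is also fair to object that dropping the as-treated test would not by itself isolate PRF at 6 months. Crossover raises the intention-to-treat PRF arm too, and a PRF-only row in a table is the same outcome-selected group. Both objections stand, and the fix has to cover them.

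**Conclusion.** The point holds in conditional form, for a secondary analysis after week 8. If as-treated means procedure received and is applied at 6 months, PRF success is biased upward at any uptake above zero. With the plan's 30% and 70% rates, lasting PRF response and uptake of 25% to 100%, the excess is about 6 to 70 points. Where it falls in that range depends on uptake, which the documents do not give. With 60% of responses maintained, the excess is 10 points at 50% uptake (28% against 18%) and 42 points at full uptake (60% against 18%).

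The figures use responder proportions, the basis of the success definition and the sample size. The same selection would act on pain scores, but the article gives no standard deviation from which to size that effect. As planned, neither 6-month analysis isolates the effect of PRF alone.

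**What to change.** Change the analysis text only; the crossover itself can stay as it is.

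1. Define as-treated and restrict that comparison to 8-week data collected before crossover. Make no 6-month test of PRF against neurectomy between groups defined by treatment received.
2. Present the 6-month intention-to-treat result as a comparison of strategies: PRF with optional neurectomy against immediate neurectomy.
3. If a PRF-only effect at 6 months is wanted, keep every patient randomised to PRF in the denominator and count crossover to neurectomy as PRF non-response.
4. Report any results by sequence (PRF only, PRF then neurectomy, neurectomy) descriptively, with denominators, and mark the PRF-only row as selected on outcome.

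The cost is a few sentences and the loss of one secondary test. No additional patients or visits are needed.
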